### Secondary Outcomes

Secondary outcome measures will be self-assessment of depression, anxiety, and quality of life using the MADRS-S [41], Generalized Anxiety Disorder Assessment 7-item (GAD-7) [42], and Quality of Life Inventory (QOLI) [43]. MADRS-S is a self-assessment version of MADRS, and features nine items measuring changes in mood, anxiety, sleeping patterns, appetite, concentration, initiative, emotional engagement, pessimism, and attitude towards life [38]. MADRS is designed to be particularly sensitive to treatment effects, and shows high correlations, from *r*=.80 to .94, between expert ratings and self-reports [44]. GAD-7 features seven items for assessing anxiety, and screening for generalized anxiety disorder. GAD-7 has yielded good internal consistency, Cronbach alpha .92, and a good factorial structure, 69% to 81% of variance explained [42]. QOLI features 32 items concerning 16 areas of life rated by the subject concerning importance and satisfaction. QOLI has yielded good internal consistency, Cronbach alpha between .77 and .89, as well as one month test-retest reliability, from *r*=.80 to .91 [43,45]. Participants will complete the secondary outcome measures before commencing the treatment period, immediately upon completion of the treatment, and at the 12-month follow-up.

### Analysis

The study design will allow multiple comparisons-the two treatment groups, with or without therapist contact, will be compared to the wait-list control (separately and together) at posttreatment. In all subsequent analyses, the treatment groups will include those from the control group later randomized to interventions, which will increase the statistical power. The two treatment groups will be contrasted with the control group. Further, the treatment group with therapist contact (group 1) will be contrasted with the group without therapist contact (group 2). At the 12-month follow-up, within-group comparisons will be made with previous results. A number of statistical analyses will be deployed, all of which will be analyzed by the intention-to-treat approach. Treatment outcomes will be examined using mixed-effect models, Bonferroni-correcting for multiple comparisons. This method is deemed preferable to uni- and multivariate repeated measures of variance [46]. Standard missing data analysis (eg, *t* tests, chi-square of severity and sex) will be utilized to determine if unexpected missing data due to participant drop out are random or not.

All outcome measures will be completed directly by the participants via an online interface, minimizing the risk of data loss or data distortion [47,48]. Data will be stored encrypted and in unidentifiable form using an auto-generated identification code.

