### Control Condition

The participants in the control group will be on a wait-list throughout the 10-week treatment period, and this group is expected to be inferior to the other two treatment groups. For ethical reasons the participants in the control group will gain access to the same intervention following the 10-week treatment period, albeit without therapist contact.

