### Inclusion Criteria

Participants will be included in the study if their primary difficulties are caused by chronic and severe procrastination. However, since procrastination is not considered a psychiatric condition there will be no need to utilize diagnostic criteria (ie, Diagnostic and Statistical Manual of Mental Disorders Fourth edition, DSM-IV) [35], or a structured clinical interview (ie, Structured Clinical Interview for DSM-IV) [36]. In order to determine and evaluate the severity of procrastination several primary outcome measures will be used (eg, the Pure Procrastination Scale, PPS; the Irrational Procrastination Scale, IPS; and the Susceptibility to Temptation Scale; STS) [37]. To date, none of the primary outcome measures have clinically established cut-offs. However, greater than 32 points on the IPS have been found to distinguish more severe cases of procrastination (ie, top 25%) [1], and will therefore be used as cut-off for inclusion.

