### Primary Outcomes

Primary outcome measures will be self-assessment of procrastination using a Swedish version of the PPS [37], the IPS [37], and the STS [37]. The PPS features 12 items measuring the prevalence of procrastination, and was originally developed to improve the validity of several different procrastination scales [37]. The items used in the PPS have a reliability of .92, and the PPS shows improved convergent validity with other related measures. The IPS features nine items measuring the degree of irrational delay causing procrastination. The items used in the IPS have a reliability of .91, and the IPS correlates together with the PPS at .96, allowing them to be used as parallel forms and share validation efforts [37]. The STS features 11 items measuring the susceptibility to temptation, which can affect the ability to follow through a task or commitment. The items in the STS have a reliability of .89, and demonstrate correlation with both the PPS and the IPS. However, since none of the primary outcome measures contain established cut-offs, clinical assessment will be used to determine treatment outcome. Participants will complete the primary outcome measures before commencing the treatment period, immediately upon completion of the treatment, and at the 12-month follow-up. Participants, including those on wait-list control, will also complete the IPS each week during the treatment period, allowing continuous measurement and increasing the statistical power.

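### At 12 months the plan names only within-group comparisons and does not fix the guided-versus-unguided contrast in the originally randomised arms

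*Protocol article*

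**What the plan says.** The Analysis section of the protocol article sets out the comparisons in this order.

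- Against wait-list: the two treatment groups "will be compared to the wait-list control (separately and together) at posttreatment".
- After that: "In all subsequent analyses, the treatment groups will include those from the control group later randomized to interventions, which will increase the statistical power".
- Therapist contact: "the treatment group with therapist contact (group 1) will be contrasted with the group without therapist contact (group 2"). No time point is given.
- Final time point: "At the 12-month follow-up, within-group comparisons will be made with previous results".

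On the wait-list arm, the Control Condition section says that "participants in the control group will gain access to the same intervention following the 10-week treatment period, albeit without therapist contact". On data, the Primary Outcomes section says: "Participants will complete the primary outcome measures before commencing the treatment period, immediately upon completion of the treatment, and at the 12-month follow-up". On entry, the Inclusion Criteria section reports that "greater than 32 points on the IPS have been found to distinguish more severe cases of procrastination (ie, top 25" per cent) and adopts that value as the cut-off. The IPS is also one of the three primary outcomes, with the PPS and the STS.

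**The concern.** Once the wait-list has crossed over, no untreated arm remains. The guided and unguided arms are still as randomised and are measured on every primary outcome at 12 months. Superiority of therapist contact is a stated hypothesis (Trial Objectives and Purpose), with no limit to posttreatment. Yet the only analysis assigned to 12 months compares each group with its own earlier scores.

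Two things are at stake. The long-term estimate of the effect of therapist contact may not be produced, or may be produced from a mixed comparison. And a baseline-to-12-month change may be read as lasting benefit, although part of it would appear with no treatment: people enrolled because they scored high tend to score lower when measured again.

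**Working it through.** **Which contrast survives.** The undated therapist-contact sentence can be read in two ways.

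1. It applies at posttreatment only. Then no between-group estimate is planned at 12 months.
2. It also applies at 12 months. Then the pooling rule for later analyses applies too, and former wait-list participants enter the treatment groups. Under the Control Condition section all of them join the unguided side, giving 50 v 100. The two sides then differ in therapist contact and also in a 10-week wait, and the Trial Status section puts follow-up in December 2014 for the treatment groups but February 2015 for the control group. The Analysis section speaks instead of controls later randomised to interventions, which does not agree with all of them receiving the version without therapist contact.

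Neither reading fixes guided versus unguided in the original arms.

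**Plan's own figure.** Only 3 × 50 = 150 can be reproduced. The article gives no alpha, power, effect size or SD.

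**Regression to the mean, baseline to 12 months, no treatment effect.** From the document: selection of the top 25%, IPS reliability .91, 50 per arm. Assumed: normal scores, a cut at the population's 75th percentile, the screening score serving as baseline, and 12-month correlations of .80 and .70.

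- Cut: z = 0.674.
- Mean of those selected: φ(0.674)/0.25 = 1.271 population SD.
- SD of those selected: √(1 + 0.674 × 1.271 − 1.271²) = 0.492.
- Expected fall: (1 − r) × 1.271.
- Later SD: √(r² × 0.492² + 1 − r²).
- d is the fall divided by the baseline SD (0.492), or by the root mean square of the baseline and later SDs.

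| r | Fall (population SD) | Later SD | d, baseline SD | d, averaged SD | Chance of a significant paired test, n = 50 |
|---|---|---|---|---|---|
| .91 (stated) | 0.114 | 0.61 | 0.23 | 0.21 | 48% |
| .80 (assumed) | 0.254 | 0.72 | 0.52 | 0.41 | 83% |
| .70 (assumed) | 0.381 | 0.79 | 0.78 | 0.58 | 95% |

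The last column is for a two-sided 5% paired t-test (noncentral t). The stated correlation of .96 between IPS and PPS means that selection on the IPS carries over to the PPS.

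**Posttreatment to 12 months.** With a stable true score, independent error at each visit and reliability .91, simulated means are 1.27 at baseline, 1.16 at posttreatment and 1.16 at 12 months. The fall has already happened by posttreatment, so this comparison gains nothing from it.

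**What the surviving contrast can show (50 v 50, two-sided 5% assumed, no dropout).**

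- Power: 0.32 at d = 0.3, about 0.71 at d = 0.5, 0.98 at d = 0.8.
- Detectable d at 80% power: (1.960 + 0.842) × √(2/50) = 0.56, rising to 0.62 to 0.67 with Bonferroni for two to four comparisons.
- Half-width of the 95% CI: 1.96 × √(2/50) = 0.39 SD.
- With 40 per arm (assumed 20% loss), power at d = 0.5 is 0.61.

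**The case against.** A reader might infer that the plan discards the therapist-contact contrast at 12 months and uses within-group comparison alone. The text does not say so. It says that within-group comparisons will be made, not that they replace others. The contrast stated just before has no time limit, and a condensed article may leave the time point to a fuller document. That much stands: exclusivity is an inference. It does not clear the plan, because the pooling rule is stated text and spoils the contrast on the reading that would rescue it.

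A reader might also infer that regression to the mean will pass as a durable effect. The documents do not support that in general. Earlier results include posttreatment, and the posttreatment-to-12-month comparison is largely free of the artefact. The randomised comparison with wait-list at posttreatment already removes it from the short-term effect, and the article announces no hypothesis of durability. What remains is that comparison with baseline is not excluded, and that either within-group comparison is uncontrolled for natural recovery or other treatment over the year.

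The size is open to challenge as well. Only .91 comes from the document, which does not say what kind of reliability it is or over what interval. The bias shrinks if baseline was measured again after screening, or if volunteers answering advertisements already score higher than the population, so that the cut is milder for them. Dividing by the narrowed baseline SD gives the larger d values. These points stand and are reflected in the ranges given.

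**Conclusion.** The concern holds in a limited form. The plan does not fix, for 12 months, the one randomised contrast that is still intact, and its pooling rule would contaminate that contrast if it were made then. Any within-group change from baseline is uncontrolled and biased towards improvement: about 0.11 population SD at the stated .91, more if the 12-month correlation is lower, less under the conditions named above. The figures rest on normality, a cut at the population's 75th percentile and the screening score as baseline; those beyond .91 rest on assumed correlations. Maintenance from posttreatment is a sounder within-group comparison, but it is still not a treatment effect. This concerns a follow-up analysis and leaves the posttreatment comparison with wait-list intact, so it is a correction worth making and not a flaw that undermines the trial.

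**What to change.** - State that guided versus unguided is estimated at 12 months from the planned mixed model, in the originally randomised arms only, without former wait-list participants, and with a 95% CI.
- Report within-group change descriptively, mainly as maintenance from posttreatment to 12 months, and draw no long-term efficacy claim from it.
- Reconcile the Analysis section's account of former controls with the Control Condition section. If they are analysed after crossover, show them separately.

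No new data are needed. The cost is one more contrast, which may have to join the Bonferroni family, and its power is only moderate. Leaving former controls out also gives up nominal power: about 0.71 with 50 v 50 against 0.82 with 50 v 100 at d = 0.5 (two-sided 5% assumed, before dropout). That is the price of a contrast that isolates therapist contact.

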### Sample Size

The current study includes 150 participants randomized into three groups (ie, 50 participants in each group). Since no clinical trials in the field of procrastination have been undertaken, there are no previous effect sizes to take into consideration. However, 50 participants in each group are deemed sufficient to find clinically significant differences.

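### Plain Bonferroni over four overlapping contrasts, on three unranked primary scales, either lets any-scale error rise to about 6-8% or gives up power that a closed test would keep

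*Protocol article*

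**What the plan says.** Protocol article, Primary Outcomes: "Primary outcome measures will be self-assessment of procrastination using a Swedish version of the PPS [37], the IPS [37], and the STS [37"]. No scale is put first and no rule for combining them is given. The same section states that "the IPS correlates together with the PPS at .96, allowing them to be used as parallel forms and share validation efforts". For the STS it says only that its items "demonstrate correlation with both the PPS and the IPS", without a figure. The IPS alone is also collected weekly in all groups, and under Inclusion Criteria it supplies the entry cut-off.

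Protocol article, Analysis: the two treatment groups "will be compared to the wait-list control (separately and together) at posttreatment", and "the treatment group with therapist contact (group 1) will be contrasted with the group without therapist contact (group 2"). That makes four contrasts. The correction is "Treatment outcomes will be examined using mixed-effect models, Bonferroni-correcting for multiple comparisons".

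Protocol article, Sample Size: 50 participants per group, with no effect size, alpha or power figure.

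**The concern.** The article fixes three things that fit together badly: three unranked primaries of which two are nearly the same measurement, four contrasts that repeat one another, and a correction that ignores both kinds of overlap. Whichever family the correction is meant to cover, there is a cost. A family of contrasts within each scale leaves the choice among three scales unadjusted. A family of all 12 tests spends alpha on near-duplicates.

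The cost falls on the two comparisons most likely to be small, unguided v wait-list and guided v unguided. Both are hypotheses stated under Trial Objectives and Purpose. The concern is with the method chosen, not with detail that a condensed article leaves to a fuller document.

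**Working it through.** **Inputs from the article.** Three scales; PPS-IPS correlation .96; four contrasts; 50 per group; Bonferroni.

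**Assumptions, because the article gives no figure.** Overall two-sided alpha .05; STS correlation with the other two .3 to .9; SD 1; no dropout; true standardized effects v wait-list of 0.8 (guided) and 0.5 (unguided), hence 0.3 for guided v unguided. The article gives no power calculation, so there is no figure to reproduce.

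**1. Overlap of the contrasts.** Let G, U and W be the group means. The four contrasts are G-W, U-W, (G+U)/2-W and G-U. The third is the average of the first two and the fourth is their difference, so there are two dimensions, not four. The pooled contrast correlates .87 with each single wait-list contrast. The two single ones correlate .5 with each other.

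**2. Family-wise error with all nulls true** (simulation of the 12 correlated z statistics, PPS-IPS .96, STS .3-.9):

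| Bonferroni family | Per-test alpha | Error |
|---|---|---|
| 4 contrasts, one scale | .05/4 = .0125 | 3.6% |
| 4 contrasts per scale, any of 3 scales | .0125 | 5.9-7.9% |
| 3 scales per contrast, any of 4 contrasts | .05/3 = .0167 | 7.6-10.2% |
| All 12 tests | .05/12 = .0042 | 2.2-2.9% |

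**3. Power on one scale, single post-treatment comparison.** The standard error of a two-group difference is sqrt(2/50) = 0.20. Power is about Phi(d/0.20 - z), with z = 1.960 (.05), 2.498 (.0125) and 2.865 (.0042).

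- Unguided v wait-list, d/0.20 = 2.5. At .0042: Phi(-0.365) = 36% (34% by noncentral t). At .0125: Phi(0.002) = 50%.
- Guided v unguided, d/0.20 = 1.5. At .0042: Phi(-1.365) = 9%. At .0125: Phi(-0.998) = 16%.
- Effect detectable with 80% power, (z + 0.842) x 0.20: 0.56 at .05, 0.67 at .0125, 0.74 at .0042.

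Simulation of the alternatives under the same effects gives:

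| One scale | Bonferroni 12 | Bonferroni 4 | Holm over 4 | Closed test |
|---|---|---|---|---|
| Unguided v wait-list | about 35% | 50% | 63% | 70% |
| Guided v unguided | about 9% | 16% | 27% | 32% |

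**4. Same power, counting success on any scale** (STS correlation .5-.7). Unguided v wait-list: 50-54% with 12 tests and 65-69% with four contrasts per scale, against 70% for the closed test on one scale. Guided v unguided: about 15-16% and 25-27%, against 32%.

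**5. Validity of the closed test.** With G = W and U = W, all three means are equal. The same follows from any other pair of the four nulls; for example, G = U together with (G+U)/2 = W gives G = U = W. So either the global null is true, or at most one of the four nulls is. A global three-group test at 5%, then each contrast at 5%, therefore holds family-wise error on a scale at 5%, pooled contrast included. Simulation under the global null gives 5.0%.

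**The case against.** Several points on the other side stand.

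- Bonferroni is valid under any dependence, so conservatism is a trade-off and not an error. It also gives simple simultaneous confidence intervals.
- The Analysis section introduces multiple comparisons as group contrasts, so the 12-test family is the less natural reading. The lowest power figures belong to it.
- The 6-8% arises only if success on any one scale counts, which the article does not say. If all three scales had to succeed, no correction across scales would be needed; the article does not say that either.
- The power figures use a single post-treatment comparison. The article plans mixed-effect models with a baseline measure and weekly IPS. Assuming a baseline-post correlation of .5 to .7, the effect of 0.5 acts like 0.5/sqrt(1-.25) = 0.58 to 0.5/sqrt(1-.49) = 0.70. The 12-test power for unguided v wait-list then becomes about Phi(2.89-2.865) = 51% to Phi(3.50-2.865) = 74%.

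A reader might infer that Bonferroni halves the trial's power, from 70% to 35%. The documents do not support this. It takes the less natural family, and it sets one-scale power beside an error rate counted over any scale. On a common any-scale count the four-contrast reading loses little for unguided v wait-list (65-69% v 70%). A reader might also infer that error is uncontrolled. Within a scale it is controlled, and conservatively.

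What survives is that plain Bonferroni over linearly dependent contrasts is beaten by procedures that control the same error, and that three unranked primaries leave open which result decides.

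**Conclusion.** The point holds as a matter that should be changed, of moderate size. On the natural reading, error is 3.6% within a scale and about 6-8% across the primaries if any scale counts. On the 12-test reading it is about 2-3%, with power lost. On one scale, moving from Bonferroni over four contrasts to a closed test lifts unguided v wait-list from about 50% to 70%, and guided v unguided from about 16% to 32%.

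These figures rest on the assumed effects, two-sided 5% alpha, no dropout and an assumed STS correlation; only the .96 and the group size come from the article. For large effects the loss is small: at d = 0.8, power is 98% unadjusted and 87% at .0042. No multiplicity procedure makes guided v unguided well powered at 50 per group under the assumed difference of 0.3.

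**What to change.** **Contrasts.** Replace plain Bonferroni with a closed test on each scale: a global three-group test at 5% and, if significant, each of the four contrasts at 5%. The pooled contrast can stay a formal test.

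**Scales.** Before outcome data are analysed, do one of the following:

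- Rank one scale as primary, with the other two secondary. The IPS is a reasonable candidate because it is measured weekly in all groups and used for inclusion. A case can be made for the PPS, which the article says was built to improve validity.
- If all three stay primary, use Holm over the full set of tests in place of the scale-by-scale procedure. It controls error across scales and is never less powerful than Bonferroni.

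**Cost.** This is more than wording. Trial Status reports recruitment complete and treatment started, and the trial is registered, so a dated amendment and a registry update are needed. Ranking one scale takes primary status from two others. Simultaneous confidence intervals are less simple than with Bonferroni. No change to data collection or sample size is required.

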### Ethics

The regional Ethical Board (Dnr 2013/974-3175) has approved the current study. In the application, the following potential ethical issues were addressed. First, great consideration will be taken not to include participants suffering from any other primary diagnosis such as severe depression, suicidal ideation, or other disorders in immediate need of treatment. Should the condition of a participant deteriorate significantly during the treatment period, supervising clinicians may choose to end the participation prematurely and direct the participant to other health care services. Second, no adverse side effects of CBT interventions are assumed to occur. However, this will nonetheless be investigated by asking standard treatment side effects questions at the posttreatment measurements [49]. Third, when using the Internet to communicate and administer interventions, the privacy of the participants is of the greatest importance [50]. As mentioned earlier, participants will therefore use anonymous auto-generated identification codes to interact with a secure online interface, and only reminders will be sent to the participants’ private email.

